## Abstract

Vascular endothelium insults caused by high serum glucose levels affect the oxygen supply to tissues, via the microvascular endothelium, resulting in an increased perfusion heterogeneity. These insults may lead to the underuse of blood capillaries, while other vessels are overused and effectively overload their oxygen supply capacity, which eventually causes damages to distal parts of the peripheral nervous system. Therefore, the proprioceptive and exteroceptive feedback information will be gradually lost and contribute to a mobility reduction. This study aims to assess the efficacy of whole-body vibration (WBV) associated with strength training (ST) on lower-limb blood flow and mobility in older adults with type 2 diabetes (DM2). Methods and analyses: This is a protocol (1st version) for Pa single-blind, randomized, controlled clinical trial guided by the SPIRIT guidelines. Our sample will consist of 51 older adults with DM2 randomly allocated to three groups: low frequency WBV (16–26 Hz) associated to ST (G1), WBV sham (G2) and nonintervention control (G3). The study protocol is set for a 12-week (three times per week) schedule. Primary outcomes: skin temperature using infrared thermographic imaging (ITI); mean peripheral arterial blood flow velocity (MBF) by a handheld Doppler ultrasound (DU), and functional mobility by Timed Up and Go (TUG) test. Secondary outcomes: quasi-static posture using the DX100 BTS Smart optoelectronic system, and plantar pressure and body balance using the MPS stabilometric platform. Data will be collected and analyzed at baseline and post-intervention, considering *p*-value < 0.05 level of significance. The analyses will also be conducted with an intention-to-treat method and effect size. Dissemination: All results will be published in peer-reviewed journals as well as presented in conferences.

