### 2.7. Outcome Measurements

#### 2.7.1. Primary Outcomes

**Skin temperature**

The thermographic imaging of lower limbs will be captured by FLIR E40bx^®^ camera (FLIR^®^ Company, Wilsonville, Oregon, EUA), with thermal sensibility of 0.5 °C, light emission value of 0.987 and 160 × 120 pixels resolution. The camera will be positioned at a distance of 1 m from the regions of interest with a 90° angle (perpendicular) relative to the camera lens [49].

The volunteers will have fifteen minutes for acclimatization and rest as the body temperature comes into alignment with the room temperature. The test room temperature will be controlled at 18 °C and 23 °C with relative air humidity between 40 and 70% monitored with a precise thermo hygrometer (KT-908). All volunteers will be previously oriented to avoid pain killers or vasoactive drugs, lotions or moisturizing creams on the regions of interest, in addition to caffeine and nicotine in the 4 h before the exam [49].

After the acclimatization period, the thermal images of the interest points will be registered and, subsequently, the mean temperature will be analyzed by the thermographic software provided by the manufacturer (FLIR^®^ Tools). Table 3 shows the six regions of interest [50]. All the photographic images will be collected by one evaluator only with expertise in managing the camera.

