**Mean peripheral arterial blood flow velocity**

Mean dorsal pedal and posterior tibial arteries blood flow velocity will be measured by a handheld Doppler ultrasound (RH-BV-620VP, Guangdong, China/Mainland) with continuous sinusoidal wave emission. The skin site for the test will be coated with a water-soluble gel, and the high-frequency (8.0 MHz ± 10%) transducer will be placed at a 45° angle in relation to the blood vessel analyzed (against the flow) [44]. For measurements related to the dorsal artery of the foot and posterior tibial artery, foot dorso and distal third of the calf will be the area of reference, respectively. The volunteers will be positioned seated with supported feet and the confirmation of the most adequate site will be performed based on the audible signals generated by the Doppler device. The measurements will be expressed in centimeter per second (cm/s), using the mean of three measures of each artery with a 60 s interval [51]. All examinations will be performed by the same experienced examiner.

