### 2.9. Data Processing and Analysis

All data records will be kept under custody of LACIRTEM lab and an allocation-blind statistician will conduct all analysis using Statistical Package for the Social Science (SPSS, IBM^®^, EUA), version 23.0, with 5% (*p* < 0.05) level of significance.

Sociodemographic, anthropometric and baseline clinical data for both groups will be expressed as the mean and standard deviation for continuous variables, proportions and percentages for nominal variables. The Kruskal–Wallis H test will be used for continuous variables and Chi-square test will be used to associate nominal variables in order to verify homogeneity between baseline data among the groups. 

All analysis will be conducted in accordance with the intention-to-treat method (ITT) using the last observation carried forward (LOCF) method, which inputs baseline data at postintervention for the dropout cases [59]. Missing values due to participants’ nonattendance or withdrawal are expected in clinical trials. Continuous variables with normal distribution will be expressed as mean and standard deviation and the intra-group comparison will be performed by paired *t*-test, and the inter-group comparison by analysis of variance (ANOVA). For nonnormal continuous variables, data will be expressed in median and interquartile intervals (Q25–Q75) and compared within the groups by Wilcoxon test and among the groups by Kruskal–Wallis H test. Size effect will be calculated to support the statistical significance. 

We will also investigate and register the possible adverse events during the treatment protocol. 

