## 3. Discussion

This study presents an overview of a training program and a detailed description of the assessment methods in an older population with DM2. A properly prescribed and regularly performed physical activity is considered an essential tool for the management of DM2 and its complications [9]. However, low compliance rate to physical activity programs is one of the barriers faced by healthcare professionals, especially from the diabetic older population [60]. Therefore, new, effective, long-term and low-cost strategies to keep this population active are needed. WBV fits as a promising training modality that is feasible, practical and safe and, when combined with ST, can provide additional effects [61].

The assessment of vascular function is a primary outcome, aiming to reduce the risk of cardiovascular complications. The endothelium is essential to maintain vascular homeostasis; however, when dysfunctional, it loses its physiological properties and undergoes changes [18]. Thus, two important tools will be used, the infrared thermographic image (ITIV) and the portable vascular Doppler ultrasonography (UDV) for quantitative evaluation and mapping of these changes. ITIV is a useful method of assessment that allows the measurement and recording of the heat radiated by the skin surface, without providing ionizing radiation or physical contact [62], and UDV is a practical, relatively low-cost and sensitive method for assessing the mean blood flow in small vessels [63].

Functional mobility is also a primary outcome of this study, considering that important loss occurs during the aging process of people with DM2. Therefore, TUG is a simple and effective assessment method, for which high scores are associated with impaired balance, reduced gait speed and difficulty in activities of daily living [52].

Finally, if effective, this study will provide a nonpharmacological treatment option of innovative and scientific value.

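### Three unranked primary outcomes, nine variables on a natural reading, are all tested at p<0.05 with no decisive variable named, so the chance of a false-positive primary finding exceeds 5%

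*Protocol article*

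**What the plan says.** **Primary outcomes.** The Abstract gives "Primary outcomes: skin temperature using infrared thermographic imaging (ITI); mean peripheral arterial blood flow velocity (MBF) by a handheld Doppler ultrasound (DU", followed by "and functional mobility by Timed Up and Go (TUG) test". It does not rank them. The Discussion (section 3) confirms the equal standing of TUG: "Functional mobility is also a primary outcome of this study". The Introduction likewise puts blood flow and mobility together in the primary objective.

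**Variables within each outcome (section 2.7.1).**
- Skin temperature: "Table 3 shows the six regions of interest". None is singled out.
- Flow velocity: "Mean dorsal pedal and posterior tibial arteries blood flow velocity will be measured by a handheld Doppler ultrasound". Three readings are averaged for each artery, but the two arteries are not combined.
- TUG: one value, the mean of three trials.

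**Error rule.** Section 2.9 has a blinded statistician carry out all analyses "with 5% (*p* < 0.05) level of significance". The Abstract repeats this: "considering *p*-value < 0.05 level of significance". The between-group test is a three-group ANOVA, or Kruskal–Wallis for non-normal variables.

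**Sample size.** Section 2.4 bases the number of participants on thermography alone. It uses two proportions (G1 40%, G3 10%) and a 0.5 °C threshold for temperature asymmetry at the front of the knee.

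**The concern.** A 5% level limits the risk of error for one test. Here it is applied to several variables that all carry the label primary, and the text names no order, no adjustment and no variable that decides the trial. The hypothesis in the Introduction is that adding whole-body vibration to strength training improves lower-limb blood flow and mobility. Blood flow alone has eight candidate variables (six regions and two arteries). A chance result in one of them, in a trial of 51 people, could be reported as a positive primary outcome.

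Section 2.4 does not remove the ambiguity. It speaks of thermography as the primary outcome, yet the other two keep that status elsewhere. Its knee-asymmetry criterion also does not correspond to any of the six regions in Table 3.

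**Working it through.** The protocol gives no family-wise error figure, so there is none of its own to reproduce. (The sample-size figure in section 2.4 is a separate matter and is not used here.)

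**Inputs from the protocol**
- Level per test: 0.05 (section 2.9, Abstract).
- Named primary outcomes: 3 (Abstract).
- Primary variables on a natural reading: 6 regions + 2 arteries + 1 TUG = 9 (section 2.7.1).
- If left and right limbs were analysed separately: 12 + 4 + 1 = 17. The protocol does not state this.
- Arms: 3 of 17 participants each (section 2.4).

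**Assumptions not in the protocol**
- No true difference on any primary variable.
- Any one significant variable counts as a positive primary finding.
- The correlation among variables is not given, so a range is shown.

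**Step 1: independent tests.** The chance of at least one false positive among k tests is 1 − 0.95^k.

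| k | Calculation | Result |
|---|---|---|
| 3 | 1 − 0.95^3 | 14.3% |
| 9 | 1 − 0.95^9 | 37.0% |
| 17 (only if limbs are split) | 1 − 0.95^17 | 58.2% |

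**Step 2: correlated tests.** Regions on the same legs will be correlated, which lowers these figures. The simulation used 20,000 trials per setting, three arms of 17, and one ANOVA F test at 0.05 per variable.

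| Assumed correlation | 9 variables | 17 variables (limbs split) |
|---|---|---|
| 0.5 among all variables | 27.8% | 40.3% |
| 0.7 among all variables | 21.0% | 28.4% |
| 0.8 among all variables | 17.2% | 22.8% |
| 0.5 within an outcome, 0 between outcomes | 31.5% | 46.5% |
| 0.8 within an outcome, 0 between outcomes | 25.0% | 32.5% |
| 0.9 within an outcome, 0 between outcomes | 21.9% | 25.9% |

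**Step 3: what is being counted.** Steps 1 and 2 count any significant three-group difference, including G2 against G3 and results where G1 does worse. For a chance result favouring G1 over G2, a two-sided 5% test contributes 2.5%. With independent tests that gives 1 − 0.975^3 = 7%, 1 − 0.975^9 = 20%, and 1 − 0.975^17 = 35% if limbs are split. Correlation lowers these as well.

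**Step 4: what is left out.** Only one overall between-group test per variable is counted. Section 2.9 also plans paired tests within groups, which for nine variables in three arms is 9 × 3 = 27 further tests.

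**The case against.** The strongest reply is that this is a condensed article and that a multiplicity procedure or success rule may stand in an analysis plan not shown. That is fair as far as silence goes: a missing adjustment would not by itself be a finding. What remains is what the article does fix, namely three unranked primary outcomes, two of them spread over several sites, and one 5% level for all analyses. Followed as written, that rule does not hold the error for the primary family at 5%.

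Three stronger readings are tempting, and the document does not support them.

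- **A reader might infer an error rate of roughly 22% to 58%.** The upper end needs 17 fully independent tests on a left/right split that the protocol does not state for temperature or flow; it specifies bilateral evaluation only for plantar pressure. The lower end depends on an assumed correlation and is not a floor: 17% and 14% are also obtainable.
- **A reader might infer that these percentages are the chance of falsely claiming a vibration benefit.** They are not. Step 3 shows the smaller figures for that specific error, and TUG could not support a blood-flow claim in any case.
- **A reader might infer that a single significant region makes the trial positive under the plan.** The protocol states no success rule. It leaves that possibility open but does not adopt it.

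The count of nine is also a reading. Section 2.7.1 does not say whether regions are pooled. The documented minimum is three, which still gives 14% if the tests are independent.

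**Conclusion.** The point holds. With three unranked primary outcomes and one 5% level for all analyses, the chance of at least one false-positive primary finding is about 14% for one independent test per named outcome and 37% for nine independent tests. It is roughly 17% to 28% for nine variables with a common correlation of 0.8 down to 0.5. Figures up to 58% apply only if limbs are analysed separately and all tests are independent.

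All of this assumes no true effect, takes any one significant result as a positive primary finding, and counts differences between any groups in either direction. The correlations are assumptions. The exact size is therefore uncertain, but none of the settings examined brings the rate down to 5%. The matter should be corrected before analysis.

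**What to change.** 1. Name one summary variable for each primary outcome: for example, one defined thermography summary, one flow-velocity summary over both arteries, and mean TUG. State how left and right limbs enter each.
2. Make G1 against G2 the primary contrast. Both arms receive the same strength training (section 2.6), so this comparison matches the hypothesis in the Introduction.
3. Control the family-wise error at 5% across the three tests. Holm keeps the outcomes co-equal, in line with the primary objective: the ordered p-values are compared with 0.05/3 = 0.0167, then 0.05/2 = 0.025, then 0.05, stopping at the first that fails. A pre-specified fixed order at the full 5% is the alternative.
4. Report individual regions and arteries descriptively with confidence intervals.
5. Do not describe the thermography summary as the outcome the trial was sized on. Section 2.4 sized on proportions for G1 against G3, with a knee-asymmetry threshold.

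The cost is wording in the protocol and analysis plan, with no new data. Under Holm, the smallest p-value faces a stricter threshold, which reduces power. Under a fixed order, outcomes after the first non-significant one cannot be claimed as confirmed, and an order that puts TUG last would make mobility depend on the blood-flow results.

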## 1. Introduction

The natural course of aging is characterized by a progressive decline in multi-organ function that entails metabolic changes and sarcopenia [1]. However, under stress (physical and/or mental), these changes can affect homeostatic mechanisms and organic response, which decreases the capacity for storage, defense, and adaptation [2]. This imbalance generated by increased levels of free radicals and decreased antioxidant potential (deficiency of vitamins and other antioxidants) causes structural and functional oxidative damage to macromolecules, thus making them susceptible to develop pathological processes. [3,4] Among these processes, diabetes mellitus (DM) stands out for its high rate of morbidity and mortality, as well as for its association with the increase in polypharmacy and its risks of interaction, common in the elderly [5,6].

DM is an emerging global public health issue of the 21st century [7]. It is estimated that 425 million adults are affected by this disease worldwide; 12.5 million of them in Brazil [8], resulting in high social and economic burdens. Healthcare costs related to DMI were estimated between 1.197 and 6.73 billion USD worldwide and 22 billion USD in Brazil in 2015 [9].

DM involves a group of metabolic disorders marked by high blood glucose levels resulting from insufficient insulin production and/or action [10]. Among the several clinical phenotypes, type 2 diabetes (DM2) accounts for the most cases (90 to 95%) [9] and there appears to be a higher incidence in older men [11].

Chronic hyperglycemia can result in damage, dysfunction, and multi-organ and system failures, mainly, related to microcirculation [5]. Functional and structure changes in the vascular endothelium compromise perfusion regulation and consequently, may prejudice the oxygen supply to peripheral tissues [12]. This heterogeneity in perfusion is due to under-utilization of a few capillaries, whereas other capillaries are overused and thus overload [13]. 

Additionally, sub-perfusion and tissue hypoxia generate progressive damage to somatic nerve fibers (sensitive and motor) and to autonomous nervous system [14], which may cause posture instability [15], loss of balance [16], limited mobility [17], and consequently poor quality of life. Therefore, the assessment of regional or specific early perfusion is presented as an important predictor of cardiovascular diseases and can be performed noninvasively using infrared thermography and Doppler ultrasound [7].

Evidence has shown that regular physical activity is an important ally for the endothelium function recovery [18]. Among the physical activity alternatives, it is well established that strength training (ST) has several benefits for the vascular function, since muscle contraction stimulates an increase in glucose uptake by muscle cells [19].

The whole-body vibration (WBV) training program is an alternative for a safe, effective, and low-cost exercise, which can present a satisfying compliance by previously sedentary patients [20,21]. It is generally assumed that vibration stimulates muscle spindles that responds with tonic vibration reflexes thereby enhancing muscle activity [21,22,23]. In the literature, two studies identified a significant blood flow increase in DM2 patients undergone vibration [24,25]. Moreover, two systematic reviews showed positive outcomes related to WBV on glycemic control and other risks associated with diabetes [26,27].

On the other hand, when WBV is associated with ST, a few studies reported substantial positive effect on musculoskeletal response in older women [28] and in untrained adults [29,30]. In the meantime, the evidence for possible additional benefits from this combination for the recovery of endothelial function in diabetics are scarce.

Based on the above considerations, this paper presents a detailed protocol for a single-blind, randomized, controlled clinical trial guided by the SPIRIT (Standard Protocol Items: Recommendations for Interventional Trials) guidelines [31], which aims to identify additional effects of WBV associated to ST. The results will follow CONSORT (Consolidated Standards of Reporting Trials) recommendations for nonpharmacological interventions [32]. The objectives of this study are, primarily, to assess the efficiency of WBV associated with ST on lower-limb blood flow and mobility of older adults with DM2 and, secondly, to verify responses to semi-static position, plantar position and stance. 

Our hypothesis is that the addition of WBV to ST enhances benefits in lower-limb blood flow and mobility of older adults with DM2.

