### 2.4. Sample Size

The sample size was based on the primary outcome of lower-limb blood flow circulation evaluated by infrared thermographic imaging (ITI). A minimal clinically important difference for skin temperature asymmetry on the knee anterior region is over 0.5 °C [37]. Based on data from a pilot study, two proportions were compared (G1 = 40% and G3 = 10%), considering power of 80% to detect differences between groups and 5% level of significance. The following formula was used:n = [(Z*α*/2 + Zβ)^2^ P(1 − P)]/(P − Po)^2^

According to the calculation in [38], a sample of approximately 15 volunteers per arm would be necessary. We expect a realistic drop-out rate of about 20%; therefore, 17 volunteers are estimated to be enrolled in each group (total of 51 volunteers).

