### 2.5. Randomization and Blinding

The volunteers will be randomly assigned to one of the three arms: low-frequency WBV (16–26 Hz) associated with ST (G1), WBV sham associated with ST (G2), and an untreated group (G3). A researcher not involved in the study will perform the volunteers’ randomization using the webpage www.randomization.com (accessed on 20 January 2018). and subsequently, their allocation will be through opaque, sealed, sequentially numbered envelopes assigned to the interventions management team. 

The envelopes will be opened, in order, by the intervention team that will reveal the type of treatment to be assigned to the volunteers.

The study nature will prevent blinding of the intervention team and volunteers. However, the researcher that conducts the initial and final assessment of the outcomes and the statistician will be blinded to the allocation.

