### 2.6. Intervention

The training protocol will last for 12 weeks (3 months) and comprise three times a week for 60 min each session. Before each session, the volunteers in arms G1 and G2 will be instructed by the intervention team to perform basic warming and stretching exercises accordingly to the Ramos protocol [21]. 

The ST consists of two sets (A and B) each to be performed alternately [39,40], as shown in Table 1, in accordance with recommendations of the American College of Sports Medicine (ACSM) for older adults [41] and Brazilian Diabetes Society (Sociedade Brasileira de Diabetes—SBD) [9]. A frequency of three days a week will be applied, very light to light intensity (40% to 50% of the test of a maximum repetition—1RM) and seven exercises involving the main muscle groups. In the 1RM test, a familiarization will be performed (pre-session), starting with 10% of body weight, progressing to the maximum lifting capacity, for a maximum of 5 attempts with an interval of 30 s between each attempt. The test will be performed bilaterally, starting with the nondominant side [42].

In addition, dumbbells and grounded muscle training equipment with different loads (Mega II, Marca Movement) will be used. The training will start initially with two sets of eight repetitions (1st to 4th week), progressing to two sets of twelve repetitions (5th to 8th week) and, finally, two sets of fifteen repetitions (9th to 12th week) [9,41]. The rest between sets will be sixty seconds and the load will gradually increase according to a good exercise performance. The strength training protocol will be applied to arms G1 and G2 equally.

Next, WBV will be applied through the Kikos P204–110v platform (Kikos Fitness, São Paulo-SP, Brasil), which has an oscillatory lateral vibration direction. The vibrating platform baseplate is slip-resistant for better safety during the training [7]. The amplitude (the vertical displacement of oscillatory motion) will be determined by the distance between both feet on the surface of the platform, ranging from approximately 2.0 mm to 5.0 mm [43]. A gradual increased in vibration frequency (the number of cycles of oscillation) and exposure duration was performed to avoid an early muscle activity decrease [44,45,46]. Vibration frequency and time spent between use and rest per week are described in Table 2.

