## 4. Strengths and Limitations of the Study

The development of a protocol study for a single-blind, randomized, controlled clinical trial that is able to identify whether whole-body vibration (WBV) provides additional benefits to strength training (ST) in lower-limb blood flow and mobility in older adults with type 2 diabetes mellitus (DM2). The vibrating platform is safe equipment, easy to handle and low-cost, which minimizes the need for conscious effort; therefore, it is most suitable for obese and sedentary patients. This new tool may be a strategy for lower-limb blood flow assessment associated with infrared thermographic imaging analysis and mean peripheral arterial blood flow velocity evaluated by a handheld Doppler ultrasound to identify physiological changes. The limitations are an absence of clinical outcomes such as quality of life, and that the vibration sham (a device emitting a similar noise to WBV) can produce physiological effects due to static squatting.

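### The hypothesis concerns what vibration adds to strength training (G1 vs G2), but the sample size and 80% power rest on G1 vs untreated G3, and the named between-group tests do not by themselves test the hypothesis

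*Protocol article*

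**What the plan says.** Three statements pose the same question. The hypothesis at the end of section 1 reads: "Our hypothesis is that the addition of WBV to ST enhances benefits in lower-limb blood flow and mobility of older adults with DM2". The same section describes a trial "which aims to identify additional effects of WBV associated to ST". Section 4 says the trial is "able to identify whether whole-body vibration (WBV) provides additional benefits to strength training (ST").

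The arms, in section 2.5, are "low-frequency WBV (16–26 Hz) associated with ST (G1), WBV sham associated with ST (G2), and an untreated group (G3"). On the shared component, section 2.6 says: "The strength training protocol will be applied to arms G1 and G2 equally". The same section has sham volunteers hold the same squat for an equivalent time, and has G3 carry on with usual diabetes management without exercise.

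For the sample size, section 2.4 says that "two proportions were compared (G1 = 40% and G3 = 10"%), "considering power of 80% to detect differences between groups and 5% level of significance". It gives no rate for G2. The result is about 15 per arm, raised to 17 (51 in total).

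For the analysis, section 2.9 gives paired tests within groups, "and the inter-group comparison by analysis of variance (ANOVA") for normally distributed outcomes, and Kruskal–Wallis across groups otherwise. It singles out no pair of arms.

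**The concern.** G1 and G2 are planned to differ only in whether the platform vibrates. G1 and G3 differ in vibration, ST, static squatting, and three supervised sessions a week for 12 weeks. The protocol itself expects the other components to act: section 1 treats the vascular benefit of ST as established, and section 4 concedes that the sham squat may have physiological effects. On that reasoning, the G1–G3 difference is larger than the part due to vibration, and power computed for it does not carry over to the hypothesis.

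The named tests have a related gap. ANOVA and Kruskal–Wallis test whether all three arms are alike. They tend to reject when both trained arms differ from the untreated arm, whether or not vibration contributes. The within-group tests cannot separate vibration from ST either.

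At stake is whether the trial can answer its own question, and whether readers will take the 80% as the power for that question.

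**Working it through.** **Inputs from the protocol.** G1 = 40%, G3 = 10%, 80% power, 5% significance (two-sided by the printed Zα/2), about 15 per arm before and 17 after the dropout allowance (section 2.4). ANOVA on three arms (section 2.9).

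**Inputs assumed.** The protocol gives no SD and no G2 rate. The standardised differences (0.5, 0.8, 1.0 SD) and the G2 rates (10%, 20%, 30%) below are assumptions, shown as ranges.

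**1. The plan's own figure.** The printed formula is n = (Zα/2 + Zβ)² P(1 − P)/(P − Po)², with (1.960 + 0.842)² = 7.849.
- P = 0.40, Po = 0.10: 7.849 × 0.24/0.09 = 20.9.
- P = 0.10, Po = 0.40: 7.849 × 0.09/0.09 = 7.8.
- Mean P = 0.25 in the variance: 7.849 × 0.1875/0.09 = 16.4.

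None gives 15. The usual two-sample formula for 40% vs 10% gives 32 per arm, and power for that contrast is 47% at 15 and 53% at 17 per arm. This is a separate matter. The present point would stand even if the 15 were correct, because the contrast is G1 vs G3.

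**2. Power for G1 vs G2 on the proportion scale.** G1 = 40%, two-sided 5%, normal approximation with pooled variance under the null:

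| Assumed G2 rate | Power, 15 per arm | Power, 17 per arm | Per arm for 80% |
|---|---|---|---|
| 10% | 47% | 53% | 32 |
| 20% | 22% | 24% | 82 |
| 30% | 8% | 9% | 356 |

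The first row treats sham plus ST as no better than no treatment, the case most favourable to the plan among those shown.

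**3. Power for G1 vs G2 on a continuous scale.** Two-sample t test, non-centrality d√(n/2), 2n − 2 degrees of freedom:
- n = 17: 80% power at d = 0.99; power 29% at d = 0.5.
- n = 15: 80% power at d = 1.06; power 26% at d = 0.5.

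Pooling the error over all three arms (3n − 3 degrees of freedom) changes these detectable differences only to 0.98 and 1.05.

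**4. The omnibus test when vibration adds nothing.** Let G1 = G2 = d and G3 = 0, in SD units. The mean is 2d/3, and the squared deviations sum to 2 × (d/3)² + (2d/3)² = 2d²/3, so λ = n × 2d²/3. For n = 17 the F test has 2 and 48 degrees of freedom:
- d = 0.8: λ = 17 × 0.64 × 2/3 = 7.25; rejects in 64% of trials.
- d = 1.0: λ = 17 × 1.00 × 2/3 = 11.33; rejects in 84% of trials.

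At n = 15 the figures are 58% and 79%.

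**5. What the 64% and 84% mean.** They are the power to find a real difference between trained and untreated arms. In simulations of the same two cases at 17 per arm, a significant F test followed by an unadjusted two-sided 5% G1–G2 test falsely favoured vibration in about 2.4% to 2.5% of trials.

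**The case against.** **Follow-up tests may exist elsewhere.** Pairwise comparisons after a three-arm omnibus test are commonly left to an analysis plan or full protocol, and neither is shown. A reader might infer from section 2.9 that the trial will claim a vibration benefit from a significant ANOVA, and might read 64% to 84% as a false-claim rate. The protocol supports neither. It does not say that the omnibus result will be read that way, and it does not rule out a G1–G2 comparison. With such a comparison the false-positive rate is ordinary (step 5). This part of the objection stands. It does not reach section 2.4, since no follow-up test changes the contrast on which the power was computed.

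**The objective may mean the package.** The primary objective in section 1, and the aim in the Abstract, refer to vibration associated with ST. Read as the combined programme against no treatment, G1 vs G3 is relevant. That reading is possible, but the hypothesis and section 4 then have no matching power statement. The passages need reconciling either way.

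**G1 vs G2 is not perfectly clean.** Section 2.5 says volunteers cannot be blinded, so this contrast may also carry expectancy effects. That is true. It is still the only contrast in the design that holds ST and squatting constant.

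**Wording does not create power.** This is also true. Renaming the contrast makes the limitation visible but does not remove it.

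**Conclusion.** The point holds as a mismatch between hypothesis, sizing and named test. The 80% power in section 2.4 concerns G1 vs G3 and does not apply to the stated hypothesis. For the contrast that does, 17 per arm gives 80% power only for about 1.0 SD (about 1.06 SD with 15 completers), and 29% power for an assumed 0.5 SD. On the proportion scale, power at 17 per arm runs from 53% down to 9% as the assumed G2 rate goes from 10% to 30%.

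The omnibus tests in section 2.9 can be significant through ST alone. The 64% and 84% rest on assumed effects, and would mislead about vibration only if the F test were read without a G1–G2 comparison. The absence of a named post hoc procedure is not itself the finding.

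**What to change.** - **Primary contrast.** Name G1 minus G2 as the primary contrast for each primary outcome, estimated with a 95% CI from the model fitted to all three arms. Keep the omnibus test, G1–G3 and G2–G3 as supportive.
- **Section 2.4.** State that the 80% power calculation concerns G1 vs G3 and not the hypothesis. Add what the planned size can detect for G1–G2: about 1.0 SD with 17 per arm and about 1.06 SD with 15 completers (80% power, two-sided 5%), with 29% power at 17 per arm for an assumed 0.5 SD.
- **Claims.** Limit statements about vibration to the G1–G2 contrast, including the one in section 4.
- **Objective.** Reconcile the primary objective in section 1 and the Abstract with the hypothesis, so that both point to the same contrast.

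The cost is wording and a less favourable stated detectable effect; no extra volunteers are needed to make these changes. Powering G1–G2 at 80% would be a larger decision: step 2 gives 32 to 356 per arm before dropout, depending on an assumed G2 rate. The three primary outcomes remain, so this change does not by itself define a single primary test.
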